## Abstract

**Background:**

Comprehensive caries care has shown effectiveness in controlling caries progression and improving health outcomes by controlling caries risk, preventing initial-caries lesions progression, and patient satisfaction. To date, the caries-progression control effectiveness of the patient-centred risk-based CariesCare International (CCI) system, derived from ICCMS™ for the practice (2019), remains unproven. With the onset of the COVID-19 pandemic a previously planned multi-centre RCT shifted to this “Caries OUT” study, aiming to assess in a single-intervention group in children, the caries-control effectiveness of CCI adapted for the pandemic with non-aerosols generating procedures (non-AGP) and reducing in-office time.

**Methods:**

In this 1-year multi-centre single-group interventional trial the adapted-CCI effectiveness will be assessed in one single group in terms of tooth-surface level caries progression control, and secondarily, individual-level caries progression control, children’s oral-health behaviour change, parents’ and dentists’ process acceptability, and costs exploration. A sample size of 258 3–5 and 6–8 years old patients was calculated after removing half from the previous RCT, allowing for a 25% dropout, including generally health children (27 per centre). The single-group intervention will be the adapted-CCI 4D-cycle caries care, with non-AGP and reduced in-office appointments’ time. A trained examiner per centre will conduct examinations at baseline, at 5–5.5 months (3 months after basic management), 8.5 and 12 months, assessing the child’s CCI caries risk and oral-health behaviour, visually staging and assessing caries-lesions severity and activity without air-drying (ICDAS-merged Epi); fillings/sealants; missing/dental-sepsis teeth, and tooth symptoms, synthetizing together with parent and external-trained dental practitioner (DP) the patient- and tooth-surface level diagnoses and personalised care plan. DP will deliver the adapted-CCI caries care. Parents’ and dentists’ process acceptability will be assessed via Treatment-Evaluation-Inventory questionnaires, and costs in terms of number of appointments and activities. Twenty-one centres in 13 countries will participate.

**Discussion:**

The results of Caries OUT adapted for the pandemic will provide clinical data that could help support shifting the caries care in children towards individualised oral-health behaviour improvement and tooth-preserving care, improving health outcomes, and explore if the caries progression can be controlled during the pandemic by conducting non-AGP and reducing in-office time.

*Trial registration*: Retrospectively-registered-ClinicalTrials.gov-NCT04666597-07/12/2020: https://register.clinicaltrials.gov/prs/app/action/SelectProtocol?sid=S000AGM4&selectaction=Edit&uid=U00019IE&ts=2&cx=uwje3h. Protocol-version 2: 27/01/2021.

**Supplementary Information:**

The online version contains supplementary material available at 10.1186/s12903-021-01674-1.

## Background

Caries is a highly prevalent disease that has a global impact on health and well-being that is highly ranked. Untreated caries has been recently reported as the most prevalent global-burden-disease (GBD) condition, with an age-standardised prevalence of 34% in permanent teeth and 7.8% in primary teeth [1]. Traditional approaches to the assessment and management of dental caries were founded on a dichotomous determination of disease, and reparative approaches. As understanding of the disease process has developed alongside novel approaches to prevention and management, modern approaches emphasise caries as a process of demineralisation of the tooth surface, which can be reversed in its earliest stages, as well as the importance of prevention of the disease process [2, 3].

Though clinical studies have found that caries management systems aimed at preventing and controlling caries at the individual- and tooth-surface level, can achieve successful health outcomes and patient satisfaction with potential long-term cost-effectiveness [4–7], capability, opportunity and motivational barriers, amongst others, have been reported to affect the adoption of best clinical practice behaviors [8]. While the recently launched caries care system, CariesCare International (CCI) [9] was designed to help overcome these, its effectiveness in the control of caries progression has not yet been demonstrated.

CariesCare International was developed in 2019 as a health outcomes-focused patient-centered risk-based approach to caries management designed for the dental practice [9]. Its practice-friendly consensus guide, derived from the International Caries Classification and Management System (ICCMS™) [11, 11], promotes best practice as informed by the best available evidence to control the caries process and maintain oral health in their patients it advocates the ‘4D cycle’. This include: 1D: Determine Caries Risk; 2D: Detect caries lesions, stage their severity and assess their activity status; 3D: Decide a personalized care plan, and 4D: Do the preventive and tooth-preserving care, which includes risk-appropriate preventive care, control of initial non-cavitated lesions, and conservative restorative treatment of deep dentinal and cavitated caries lesions.

At the beginning of 2019, the Caries OUT collaboration were ready to start a 12-month multicentre pragmatic randomized clinical trial (RCT) in schoolchildren to compare the control of individual and tooth-level caries progression of the CCI system versus standard care. At that point, the collaboration had (1) achieved ethical approval via the leading centre, (2) recruited a number of clinical institutions, (3) obtained a partial funding from the IADR Regional Development Program for the Latin American Region (IADR RDP LAR), (4) prepared training material, and (5) planned training for researchers to start the study.

On March 11, 2020, the World Health Organization declared the global spread of coronavirus disease (COVID-19) a pandemic [12]. SARS-CoV-2 is a respiratory airborne virus that may be transmitted through dental procedures producing aerosols, either because virus remains suspended in the air or through contamination of inanimate surfaces. Aerosol generating dental procedures (AGPs) therefore are considered a potential source of infection for susceptible individuals [13, 14]. Consequently, elective dental procedures were stopped in the USA in March 2019 [15] and many other locations worldwide. This also led to the cancellation of many clinical dental studies, mainly randomized controlled trials, including the Caries OUT study as previously conceived.

However, since May 2019 the Caries OUT collaboration have discussed how meaningful research in the current restricted clinical environment might still be conducted to inform caries management in children. This was felt to be particularly important given restrictions in current dental care which may contribute to an increase in the caries burden within the child population, especially in countries with higher health inequalities [16]. The collaboration worked to develop an adapted CCI Caries OUT single-group study, which would be viable without placing participants at increased risk of SARS-CoV-2 transmission. Amendments to the previous protocol includes managing caries in children with a 4D-cycle CCI adapted for the pandemic era, without AGPs [16–22], and reducing in-office time/appointments [16, 18, 19, 23] (Fig. 1). Processes during caries management which do not contribute to generating potentially contaminated droplets or aerosols, amongst other things include: air-drying only with cotton rolls/gauze for the visual detection (2D), isolating only with cotton rolls, cleaning the tooth surfaces only with toothbrushing by child/parent before the appointment and in the clinic with cotton rolls/gauze (2D and 4D). Avoidance of operative care and managing caries risk include the following non-operative care (NOC) options (4D): 5% NaF varnish, 30% silver diamine fluoride (SDF), high-viscosity glass ionomer atraumatic-restorative-treatment (ART) sealants [9, 16–22, 24]. For cavitated caries lesions, either NOC or tooth-preserving operative care (TPOC) with Hall technique (for primary teeth) and ART are options (4D) [9, 16–22, 24–27]. Teledentistry text messages or videocalls can contribute to reducing in-office time/appointments [16, 18, 19, 23, 28]; these approaches can be used for the assessment of the caries risk (1D) as well as for its management via advising on home-care approaches (4D), and with oral-health behaviour change strategies focusing on toothbrushing and dietary habits [9, 29–34].

**Fig. 1 Fig1:**
[figure not shown]
Caries OUT Pandemic-adapted CCI 4D-cycle

Thus, the Caries OUT collaboration, with agreement from each of the institutions and funding bodies, proposed a revised research plan to conduct a clinical study with only one arm assessing a pandemic-adapted CCI system. The immediate benefits of such a study may be the training and empowerment of researchers/staff/dental practitioners to offer safe and appropriate caries care to children during the current COVID-19 epidemic and thus contribute to reducing the burden of caries which might otherwise increase. The aim of this 12-month multicentre single-group interventional study is to assess in children the caries-control effectiveness of a pandemic-adapted CCI protocol (non-AGP and reduced in-office appointments’ time), in terms of child-level and tooth-level control of caries progression; acceptability of care to parents and dentists; and change in children’s oral health behaviours.

## Methods/design

The design and report of this clinical trial protocol follows the Standard Protocol Items: Recommendations for Interventional Trials (SPIRIT) statement (Additional file 1). The study received approval from the Research Institutional Ethical Committee in Universidad El Bosque (PCI 2019-10718).

This is a 12-month multicentre single-group interventional study that aims at assessing in children the caries-control effectiveness of a pandemic-adapted CCI protocol (non-AGP and reduced in-office appointments’ time). The outcomes include primarily, tooth-level control of caries progression, and secondarily, child-level control of caries progression and caries risk; parents’ and dentists’ acceptability of care, and improvement in children’s oral health behaviours. Data will be collected in the 21 centres that agreed to participate, which are located in Argentina [2], Brazil [1], Colombia [7], Dominican Republic [1], France [1], Mexico [1], Perú [1], Portugal [1], Russia [1], The Netherlands [1], United Kingdom [1], United States [2], and Uruguay [1].

The study phases are based on the CCI 4D cycle (Fig. 1) and include: (1) a baseline examination (T0), corresponding to CCI steps 1D, 2D and 3D to be conducted by the examiner (E); (2) the basic management and intermediate care (CCI step 4D) to be conducted by the dental practitioner/s (DP); (3) two follow-up assessments during the 12-month care period: T1, at 5–5.5 months (3 months after end of basic management care) (E); T2, at 8.5 months, and (4) a final re-assessment at 12 months (T3) (E). The study flowchart is shown in Fig. 2.

**Fig. 2 Fig2:**
[figure not shown]
Caries OUT Pandemic-adapted CCI study flowchart

### Setting, participants and recruitment

Each centre will define where they will conduct the local single-group interventional study. This can be either in a dental school clinic, in a dental schools’ community/hospital/school children’s clinics, or if these are not available due to the pandemic, in researchers’ private practices. Invitations will be sent to these clinics and upon interest to participate, the centre coordinator will explain the study, its purposes and procedures. When and if the clinics’ authorities accept to take part, corresponding invitation and information about the study will be sent to the participants’ parents (and children), together with written consent forms (Additional file 2). Written assent forms will be included in countries where it is required and also depending on the age requirement (e.g. in Colombia for children over 6 years) (Additional file 3).

The inclusion criteria are children: (1) aged 3–5 and 6–8 years old; (2) generally healthy, and (3) have parental consent and children’s assent (if needed). The exclusion criteria include children who: (1) have major systemic diseases or major mental/physical disability; (2) their family have plans to move during the study timeline, and (3) wear orthodontic appliances. The strategies to reach the target sample size at enrolment, include the motivation of parents through the invitation, explaining the advantages of having their children receiving a caries patient-centred care and risk-based prevention, and that they will be receiving printed didactic aids to improve the child’s oral health behaviours. Children who attend a different dental practice for care during the study period will be excluded.

Written consent forms signed by parents/carers and written assent forms (when these applies) signed by children will be collected from children interested in participating before the dental examination and treatment take place and subjects will be coded to keep confidentiality.

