
T0 and T3 include full 1D, 2D and 3D assessments. For intermediate T1 and T2 follow-ups, in 1D, all receive full oral-health behaviour reassessment, while risk is fully assessed only in patients previously classified as high-risk; in low-risk, only four risk/protective factors are reassessed (twice-a-day toothbrusing with ≥ 1000 ppm F, daily free-sugar intake above 50 g, dental biofilm and presence of new caries lesions). For 2D, all patients are clinically examined only for the latter. Subsequent 3D is derived. If in T1 or T2 the patient’s risk gets classified opposite to their previous assessment, both the recall interval and the reassessment are adjusted accordingly.

Parents’ and dentists’ acceptance of dental care will be assessed by an external researcher at T1, using designed TEI questionnaires (modified from Newton & Sturmey [40]).

Costs will be assessed in terms of duration and number of appointments regarding the type of care received (assessment/reassessment; individual level: risk/behavioral management, recall; tooth-surface level: NOC, TPOC;) and taking into account if the activity has been conducted solely by the examiner/CD, solely by a hygienist or both together, and country-level economic variables will be described [41–43].

Dropout criteria of a child from the study will include: (1) voluntary withdrawal from the trial by the patient/parents; (2) not attending the reassessments and in-office/remote appointments after three phone/message reminders.

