### Outcomes

#### Primary health outcome

Mean number of tooth surfaces with avoidance of caries progression (ICDAS-merged Epi severity and/or activity).

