For the analyses at the tooth-surface level, we will exclude teeth that needed a treatment involving AGP (endodontic treatment, surgical extraction, etc.). Caries progression has been defined for this study in terms of a change from the decided and delivered tooth-surface level care (T0, after the 4D basic management) to the tooth-surface level status at the 12-month follow-up (T3) (Fig. 2), as follows: (1) from a sound surface to a caries lesion, a sealant, a filling, or a missing tooth; (2) from a sealant to a caries lesion, a filling, or a missing tooth; (3) to a more severe caries score and/or an active status (or remaining active), and (4) from a filling to a caries lesion or a missing tooth. The severity/activity caries progression will be firstly assessed through descriptive analyses (number of subjects/surfaces) and a comparison in the number of active lesions at 1 year versus baseline will be applied (Wilcoxon test or paired *t* test based on results of the Shapiro Wilk normality test). Multilevel logistic regression will also be used for the surface level data analyses, exploring the clustering of surfaces within individuals, to estimate the association among characteristics variables and the outcomes.

Parents’ treatment evaluation inventory: Comparisons of parents’ treatment acceptability will be conducted between participants classified in baseline as low vs. high risk using Independent *t* test.

Dentists’ treatment evaluation inventory: The dentists’ treatment acceptability will be described.

Oral-health related behaviour classification will be compared between assessments (T0, T1, T2, T3) and between high and low-risk patients using *t* test.

The level of significance considered for all tests will be 5%.

Analyses to handle protocol non-adherence and missing data: Data of patients who leave before the end of the study will be handled separately. A *t* test analysis will be conducted to compare the baseline mean number of surfaces with caries experience (ICDAS-merged Epi dmfs/DMFS) [35] of those children who left the study during the 1-year follow-up period with that of those who remained in the study. If they’ve left after T1 and or T2, their parents TEI will be also compared with that of those who remained, as well as the children’s oral-health behaviour classification, and the caries progression.

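### Excluding children who seek care elsewhere and setting early leavers' data apart makes the progression estimate stayers-only and open to selection bias, with no control arm to offset it

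*Protocol article*

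**What the plan says.** Four statements in the protocol article bear on this.

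- **Setting, participants and recruitment**, after the eligibility criteria: "Children who attend a different dental practice for care during the study period will be excluded".
- **Baseline and follow-up oral examinations** gives two dropout criteria. One is voluntary withdrawal; the other is "not attending the reassessments and in-office/remote appointments after three phone/message reminders". Care at another practice is not among them.
- **Statistical analysis plan**, on non-adherence and missing data: "Data of patients who leave before the end of the study will be handled separately". Two comparisons of leavers with stayers follow. The first is at baseline: "A *t* test analysis will be conducted to compare the baseline mean number of surfaces with caries experience". The second applies to children who left after T1 and/or T2 and compares the parents' TEI, "as well as the children’s oral-health behaviour classification, and the caries progression".
- **Statistical analysis plan**, definition of progression: the change from the surface-level care delivered at the start (T0, after basic management) to surface status at T3. A sound surface that becomes filled or missing counts as progression, as does a filled surface that becomes carious or missing.

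The Discussion acknowledges that comparability with a control group has been lost. Sample size and recruitment allows for 25% dropout.

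**The concern.** Eligibility rules normally rest on what is known at enrolment. This one depends on something that happens during follow-up and may be linked to the outcome. Pain, extraction and failure of a filling or sealant are secondary outcomes of the trial, and they are also ordinary reasons to see another dentist. A child who goes elsewhere in pain and returns with a new filling or a missing tooth would often count as progression under the protocol's own definition. The exclusion can take that child out of the data before the event is counted.

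Setting early leavers' data apart works the same way: a child without T3 cannot contribute to a T3 endpoint unless the analysis makes provision for it. In a two-arm trial similar losses might partly cancel in the comparison. Here the single-group estimate is the result, and the Discussion says positive results would help change the standard of care.

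**Working it through.** **1. What the rules leave in the estimate.**

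| Child | Stated handling | In the T3 progression estimate? |
|---|---|---|
| Stays, no progression | analysed | yes |
| Stays, progresses | analysed, counted as progression | yes |
| Attends another practice during the study | excluded | no |
| Withdraws or stops attending | data set apart; compared with stayers | no |

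The estimate therefore describes stayers. Stayers who progress are still counted against the intervention.

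**2. The protocol's own figures.** Inputs from Sample size and recruitment: SD 2.5, means 1.3 and 2.1 (difference 0.8), type I error 0.05, type II error 10%. With two-sided testing:

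n per arm = 2 × [2.5 × (1.960 + 1.282) / 0.8]² = 205.2, rounded up to 206. This matches.

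206 × 1.25 = 257.5, rounded up to 258. This matches. With 25% loss, 258 × 0.75 ≈ 194 children remain. From the recruitment target of 21 × 27 = 567, about 425 remain.

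**3. Size of the bias on the mean.** All-enrolled mean = (1 − d) × stayers + d × leavers, with d = 0.25. The 1.3 for stayers is borrowed from the sample-size inputs. The leaver means are assumptions; the documents give none.

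| Assumed leaver mean | All-enrolled mean | Stayers-only figure too low by |
|---|---|---|
| 1.3 | 1.30 | 0 |
| 1.7 | 0.975 + 0.425 = 1.40 | 0.10 |
| 2.1 | 0.975 + 0.525 = 1.50 | 0.20 |
| 2.9 | 0.975 + 0.725 = 1.70 | 0.40 |

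These are progressed surfaces, the scale of the planning figures. The primary outcome counts surfaces that avoid progression, so the same selection would make that figure look better.

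**4. Child-level proportion (secondary outcome).** Assume 70% of stayers avoid progression and d = 0.25.

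- Leavers 50%: 0.525 + 0.125 = 65%, so the stayers-only figure is 5 points too high.
- Leavers 40%: 0.525 + 0.100 = 62.5%, so 7.5 points too high.
- Every leaver progresses: 52.5%, so 17.5 points too high.
- Every leaver avoids progression: 77.5%, so 7.5 points too low.

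**5. Against sampling error.** The 95% half-width for the mean is 1.96 × 2.5 / √n, treating children as independent: 0.35 at n = 194 and 0.24 at n = 425. Bias equals 0.25 × (leavers − stayers). It would exceed the half-width only if leavers averaged more than 0.35 / 0.25 = 1.4 extra progressed surfaces at n = 194, or 0.24 / 0.25 ≈ 1.0 at n = 425. Recruiting more children narrows the interval but leaves the bias where it is.

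**The case against.** The case on the other side has real content.

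- **Leavers are not ignored.** A reader might infer that the baseline *t* test is the only check. It is not: for children who left after T1 or T2, caries progression itself is compared, which is the most relevant check available. This stands. But the comparisons only describe. No result of theirs changes the estimate, children lost before T1 have no follow-up to compare, and the T1 and T2 clinical examinations are narrower than those at T0 and T3.
- **Stayers are not chosen for doing well.** A reader might infer that the estimate rests on children who stayed and had good results. The documents do not support that, because new lesions, worsening and lost teeth in stayers all count as progression. Care elsewhere may also have unrelated reasons.
- **Treatment that the non-AGP approach cannot provide.** A reader might infer that children with such needs are removed. For dental emergency or endodontic need, the notes to Tables 1 and 2 provide for treatment or referral and leave out only the tooth concerned, and the Statistical analysis plan section likewise drops teeth. That stands, although the notes do not say what happens to the child if the referral is to another practice.
- **A separate SAP may exist.** Imputation and sensitivity methods may be specified there, so their absence from the article is no finding. The point rests on the two rules that the article does state.
- **The exclusion sentence is loosely placed.** It stands beside the eligibility criteria and does not say which data are removed. But it names events during the study period, so reading it as a post-enrolment exclusion is the natural course.

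**Conclusion.** The point holds in this form: the plan as written yields a stayers-only progression estimate. It is conditional on an event after enrolment and open to selection bias, with no control arm to offset it. Favourable bias is the more likely direction, because care elsewhere may follow pain, restoration failure or dissatisfaction. The documents establish neither the direction nor how often children will go elsewhere.

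The size is illustrative only. At the protocol's 25% dropout allowance and 1.3 progressed surfaces in stayers, leavers at 1.7 to 2.9 would move the all-enrolled mean to between 1.4 and 1.7. The leaver values are assumed, and the 1.3 comes from a calculation based on a study in adults. It would be tempting to express the shift as a share of the 0.8 planning difference, but that difference belongs to a two-arm comparison this trial does not make, so the ratio has no bearing on its conclusion. In the milder scenarios (0.10 and 0.20) the bias is smaller than the confidence half-width. The change should be made, but the documents do not show that the result would be overturned without it.

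**What to change.** 1. Delete the exclusion sentence as an analysis rule. Keep children treated elsewhere in follow-up, seek T3 for them, and record outside care as an intercurrent event with its date, reason and affected surfaces.
2. Include these children in the main progression analysis under the existing definition. Add a sensitivity analysis that excludes them, or only their outside-treated surfaces, since a filling placed elsewhere may reflect another dentist's threshold and not progression.
3. Make the main analysis all enrolled children, with missing T3 status handled using baseline, T1 and T2 data. Add a sensitivity analysis assuming worse outcomes in leavers. The imputation model and the size of the shift are for the trial team to choose and fix before analysis.
4. Keep the planned leaver and stayer comparisons as description, and report how many children sought care elsewhere and why.
5. Reconcile the exclusion sentence with the notes to Tables 1 and 2, so that a referral concerning one tooth does not remove the whole child from the analysis.

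The cost is rewording in the protocol and SAP and some effort to bring non-attenders to T3. The estimate may be less favourable, and it will include some effect of care given outside the trial.
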